## Outcomes

4

All participants will be asked about baseline social demographics. Data on pediatric cancer characteristic will be obtained from medical records. Both cohorts of parents receive one questionnaire each, while medical staff receive questionnaires twice, once before and once after the CM training (see Figure 2). The questionnaires refer to the objectives already mentioned above in the protocol.

**Figure 2 F2:**
[figure not shown]
Overview of the study centers in the rhine-ruhr area in Germany. The team in Herdecke, consisting of medical and psychological staff with expertise in CM as well as in pediatric oncology offers bedside counseling for patients and parents and support for on-site medical staff in all five participating pediatric cancer centers.

### Feasibility

4.1

1.Attitudes towards [ABCAM (32)], previous experience with [I-CAM-R (33, 34)] and support needs (LS (35) regarding CM of parents of children with cancer2.Number of parents who can be screened, enrolled and counseled during the study period, number of medical staff, study-related retention and dropout rates, reasons for study dropouts3.Acceptability of the CM intervention (parent intervention cohort only), assessed with the Acceptability of Intervention Measure [AIM (36)]4.Proportion of planned consultations that could be completed, feasibility of the intervention by medical staff [FIM (36)]5.Acceptability of the overall approach within the project is assessed in a targeted sample of parents and medical staff [TFA (37)].

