1.Is it feasible to recruit a sufficient number of parents/medical staff to obtain representative cohorts?2.Is it feasible to implement CM interventions in different conventional study centers according to the protocol or are there barriers that will require protocol adjustments?Secondary objectives include exploratory outcomes for evaluation:
1.Do trained parents feel better informed about the risks, benefits and safety of CM compared to untrained parents, and does this increase their ability to make better informed decisions about their use of CM?2.Do attitudes towards CM and CM usage differ between trained and untrained parents?3.To what extent does the medical staff feel relieved from administrative tasks, time pressure, and professional uncertainty by the external provision of CM counseling for parents?4.Can knowledge of the benefits and risks of CM among medical staff and their attitudes towards it be improved?The results should make it possible to successfully implement and establish CM counseling and supporting strategies in conventional pediatric cancer centers. In addition, individual CM counseling concepts will be developed for other clinics in the long term, in order to meet evidence-based IM recommendations (6).

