-Vestische Children's and Youth Hospital Datteln, Germany-Pediatric Hematology/Oncology, Dortmund Hospital, Germany-Department of Pediatrics and Adolescent Medicine, University Hospital Essen, Germany-Pediatric Hematology/Oncology, University Hospital Cologne, GermanyThe Rhine-Ruhr metropolitan area is beneficial for the fact that there are many oncological centers in a very small area, so that the treatment team can drive to them and deliver bedside counseling and support in presence. By selecting a prospective, multicenter study design, two cohorts of parents of children with a diagnosis of cancer and one cohort of medical staff from the participating pediatric oncology departments can be included. Sociodemographic data will be collected from all cohorts, with particular emphasis on the educational level of the parents, to determine whether education influences responses in the surveys. While one parent cohort will receive CM counseling, the other will serve as a waitlist cohort to be offered the respective CM counseling after the outcome assessment. Group assignment will be non-randomized by starting with a control cohort followed by the intervention cohort. After being informed about the study during the initial visit by their treating physician and signing written informed consent, parent cohorts will receive standard questionnaires three weeks after study inclusion. For the parent control cohort, the CM counseling will take place after this outcome assessment, while the parent intervention cohort will receive CM counseling before. Outcomes will be compared between groups. Medical staff will be trained in CM counseling strategies and assessed before and after the CM training. Outcomes will be compared within this group. A summary of the study design can be found in Figure 1. The active study period of recruiting is scheduled from December 2022 to end of 2027. Since there are five participating centers and a small project team, the time invested to be able to include subjects in the study will be in relation to the effort involved. For the medical staff, 100 participants are considered an acceptable and desirable number. Traveling to the study centers and maintaining contact with parents requires resources. The sample size for the survey and consultation includes 50 participants, evenly divided into two cohorts of 25 individuals each. We also expect a dropout of 10%, as parents who find themselves in such a difficult situation might also turn away.

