### Eligibility criteria

3.2

To be included in the study, participating parents must have reached the age of 18. Their children should be under 18 years of age. Both parents have to give written informed consent to participate in the study. Children who have already reached the age of 16 must give their written consent as well. All first-onset oncological diseases are considered eligible diagnoses and the children have to be undergoing conventional cancer treatment in one of the participating cancer centers. Parents who already have experience in dealing with CM can still be part of the study.

Medical staff will be eligible if they are employed in one of the participating study centers within the framework of pediatric oncology and provide written informed consent. Insufficient knowledge of German is considered an exclusion criterion for both parents and medical staff.

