### Evaluation

4.2

1.Parents satisfaction with the provision of information on the use and safety of CM and their ability to make informed decisions about the use of CM [PS-CATE (38)], [SDM (39)]2.Change in attitudes towards CM, assessed with the Attitudes and Beliefs about Complementary and Alternative Medicine [ABCAM (32)] and the benefits of potentially harmful CM procedures [I-CAM-R (33, 34)]3.Perceived stress of parents, assessed by the Perceived Stress Scale [PSS (40)], and anxiety and depression, assessed by the Patient Health Questionnaire [GAD/PHG (41)], training needs, and content and structural relief of medical staff [LS (35)]4.Attitudes towards CM procedures, assessed by the Complementary and Alternative Medicine Health Belief Questionnaire [CHBQ (42)], knowledge, query, application, reasons for non-application of CM in everyday clinical practice [LS (35)]

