Effectiveness outcomes are analyzed by examining parental satisfaction with counseling, including clarity of information on complementary medicine (CM) and its safety, using the PS-CATE and SDM-Q-9 scales. Means and standard deviations are reported, and paired *t*-tests or Wilcoxon signed-rank tests are applied to compare satisfaction scores before and after the intervention. Changes in parents’ ability to make informed decisions are assessed through pre- and post-intervention scores on the SDM-Q-9. Changes in parental attitudes toward CM, as measured by the ABCAM, and perceptions of the benefits of potentially harmful CM procedures, as assessed with the I-CAM-R, are analyzed using paired t-tests for within-group comparisons. Between-group differences, such as those between intervention and baseline cohorts, are tested using independent t-tests or Mann–Whitney *U*-tests. For medical staff, training needs and perceived burden are assessed using Likert scales, while changes in knowledge, attitudes (CHBQ), and practices regarding CM are evaluated with paired *t*-tests. Subgroup analyses are performed to identify predictors of changes in these outcomes.

To ensure psychometric robustness, subscales of multi-faceted questionnaires are averaged into non-weighted indices by calculating the mean of individual items where applicable. Cronbach's alpha coefficients are computed to assess the internal consistency of scales. All statistical tests are exploratory and conducted at a significance level of alpha = 0.05, without adjustments for multiple testing. For significant changes, additional regression analyses are conducted to identify predictors of change in predefined outcomes such as satisfaction, attitudes, or decision-making ability. Qualitative data are analyzed using thematic content analysis to complement the quantitative findings. This comprehensive approach ensures a robust evaluation of the feasibility, acceptability, and effectiveness of the intervention while identifying potential areas for refinement.

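### One I-CAM-R per parent, given after counseling in one cohort only, serves both as prior-experience measure and as evaluation outcome, so a cohort difference in CM use may be diluted and confounded by earlier use

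*Protocol article*

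**What the plan says.** All references are to the protocol article.

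- **Objective.** Secondary objective 2 (section 2) asks: "Do attitudes towards CM and CM usage differ between trained and untrained parents". It names no instrument.
- **Number and timing of assessments.** Section 4: "Both cohorts of parents receive one questionnaire each". Section 3.1: "parent cohorts will receive standard questionnaires three weeks after study inclusion". The control cohort is counseled after that assessment, whereas "the parent intervention cohort will receive CM counseling before". Cohorts are filled one after the other, without randomization.
- **First role of the I-CAM-R.** Section 4.1, item 1, uses it for "previous experience with [I-CAM-R (33, 34)] and support needs" regarding CM.
- **Second role of the I-CAM-R.** Section 4.2, item 2, uses it as an evaluation outcome for "the benefits of potentially harmful CM procedures [I-CAM-R (33, 34".
- **Who is eligible.** Section 3.2: "Parents who already have experience in dealing with CM can still be part of the study".
- **Analysis.** In section 4.6, perceptions of such benefits, "as assessed with the I-CAM-R, are analyzed using paired t-tests for within-group comparisons". Between-cohort differences are tested with independent t-tests or Mann–Whitney tests.

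**The concern.** The two roles look in opposite directions. A descriptor of previous experience should cover the time before counseling, and an outcome should cover the time after it. Here one administration has to supply both, and in the intervention cohort it comes after counseling.

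Counseling cannot change what a parent did before it. If the use items reach back past counseling, a parent who gave up a product because of the advice still reports having used it and looks the same as a control parent who carries on. That pulls the comparison toward no difference.

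The cohorts are also sequential. If their earlier habits differ, that difference enters the same answer and can mimic or hide an effect. No prior-use value collected before counseling is described that could be used to adjust for it.

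At stake is whether secondary objective 2, as far as it concerns use, can be read from the data.

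**Working it through.** **1. Is there another parent measure of use?** Sections 4.1 and 4.2 also list for parents the ABCAM (attitudes), LS (support needs), AIM and TFA (acceptability), PS-CATE and SDM (satisfaction with information, decision-making), PSS (stress) and GAD/PHG (anxiety, depression). None of these evidently records use. The interview guide (Table 1) asks parents how far they use CM, but section 4.4 plans parent interviews only in the intervention cohort, so they give no cohort comparison.

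**2. Does the planned analysis separate the periods?** No. The paired tests in section 4.6 need two measurements per parent, and section 4 provides one. That mismatch is a separate point. Here it means only that the between-cohort comparison is left.

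**3. How large could the dilution be?** The article states no figure to reproduce: no recall period, share of prior users, expected use or power. What follows is illustration under stated assumptions.

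Assumptions:
- A parent counts as a user if CM was used before or after counseling (in controls, the corresponding time).
- A share q used CM before, equal in both cohorts.
- Later use is 40% in controls and 10% in the intervention cohort, independent of earlier use.

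Reported use = q + (1 − q) × later use, so the observed difference = (1 − q) × (0.40 − 0.10).

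Power uses the normal approximation for two proportions at two-sided alpha 0.05. Section 4.6 gives alpha without sidedness. The sample sizes are 25 per cohort as planned, and 22 after the 10% dropout in section 3.1 (25 × 0.9 = 22.5, rounded down).

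| Prior users q | Controls | Intervention | Difference | Power, n = 25 | Power, n = 22 |
|---|---|---|---|---|---|
| 0% | 40% | 10% | 30 points | 70% | 64% |
| 20% | 52% | 28% | 24 points | 41% | 36% |
| 50% | 70% | 55% | 15 points | 19% | 17% |
| 70% | 82% | 73% | 9 points | 11% | 11% |

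Check for q = 50%: 0.5 + 0.5 × 0.40 = 0.70; 0.5 + 0.5 × 0.10 = 0.55; difference 0.15.

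The first row also describes a form whose recall starts at counseling: earlier use is not counted, and nothing is lost. If later users are mostly people who used before, independence fails and the loss is greater than shown.

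**4. How large could the confounding be?** Keep the same rule but let prior use differ, for example 50% in controls and 30% in the intervention cohort. With no counseling effect (later use 40% in both), reported use is 0.5 + 0.5 × 0.40 = 70% versus 0.3 + 0.7 × 0.40 = 58%, a 12-point difference from earlier habits alone. Reverse the prior shares and restore the 40% versus 10% effect: 0.3 + 0.7 × 0.40 = 58% versus 0.5 + 0.5 × 0.10 = 55%. Only 3 of the 30 points remain visible.

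**The case against.** **Questionnaire detail.** Recall period and item wording are commonly left to the full protocol or the form, and the I-CAM-R as used may already have separate items. This stands in part: a missing recall period alone would be no finding. What remains is that the article itself gives one post-counseling administration both roles and describes no separation. If the form already separates the periods, the sponsor need only say so.

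**Use is not the stated I-CAM-R outcome.** Sections 4.2 and 4.6 speak of benefits, or perceived benefits, of potentially harmful procedures, and use is not among the four hypotheses in section 4.3. This stands as a limit. A perception reported at three weeks can reflect counseling and need not be diluted by earlier use. The point therefore concerns the use part of secondary objective 2, for which the I-CAM-R as use measure is an inference.

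**Little prior use may exist.** Children have first-onset disease and families hear of the study at the initial visit, so use alongside cancer treatment may begin near inclusion. This is possible. The article gives no share of prior users; it only admits them.

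**Stronger readings.** A reader might infer that earlier use swamps later use, that a difference cannot appear, or that the objective cannot be answered. The article does not support this: the range includes no dilution at all, and equal prior use shrinks a contrast without removing it under the model above. A reader might also scale the effect by the part of a recall period after inclusion (3 of 13, 26 or 52 weeks: 23%, 12%, 6%). Those are time shares. An any-use indicator shrinks with the share of prior users.

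**Conclusion.** The point holds in limited form. One I-CAM-R, completed three weeks after inclusion and after counseling in the intervention cohort only, is both the prior-experience descriptor and an evaluation outcome. It is the only listed parent questionnaire that evidently captures use. As described, use before counseling cannot be told from use after it, so a cohort difference in use may be diluted by prior users and confounded by differing habits of the sequential cohorts.

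The size is unknown. It runs from no dilution, if recall is confined to the time since counseling, to a fall from 30 points to 24, 15 or 9 with 20%, 50% or 70% prior users. The latter rests on an assumed 40% versus 10% later use, independence from earlier use, and counting use in either period.

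The objective is secondary and the tests exploratory, so this is a worthwhile, cheap improvement and does not undermine the feasibility aims.

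**What to change.** 1. **Record prior CM use separately.** Preferably ask for it with the baseline sociodemographic items at inclusion, before counseling. If those items are collected only in the three-week form, add a separate column there for use before inclusion, and state that the intervention cohort recalls it after counseling. Counseling may alter recall or disclosure, so this fallback is not a clean baseline value.
2. **Fix the reference period of the three-week use items** to current use or use since inclusion, and compare cohorts on these items only.
3. **Use prior use** as the experience descriptor in section 4.1 and as an adjustment covariate for the use comparison, with the caveat above if it was recalled.
4. **Name the measure.** State that these items answer the use part of secondary objective 2 and which I-CAM-R items serve each role.
5. **Give both cohorts the same version.** Because the control cohort comes first, a form changed between cohorts would add a further difference.

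The cost is a few items or one response column, slightly more burden on parents, and a departure from the published response format that must be reported. No extra visit is needed with the added column. Asking at inclusion adds a short contact if none is already planned.

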### Secondary outcome

4.4

In addition to quantitative data, qualitative data will be assessed using semi-structured interviews of the parent intervention cohort and medical staff. In the *a priori* categorization, gender and age characteristics are taken into account and, in the case of medical staff, also their job description or position in the organization. To ensure the interviewees’ initiative was respected, each interview was limited to 20 min, with a primary focus on identifying barriers to implementation. The pre-developed interview guide shown in Table 1 is intended to identify barriers to the implementation of the CM intervention. Results of the qualitative analysis will be used to improve the CM training and counseling sessions, if necessary, as well as the questionnaire.

**Table 1 T1:** Semi-structured interview guide for parent interviews and interviews with medical staff.

Overview	Content	Parents	Medical staff
Introduction	Welcome and data protection Introduction of the interviewer Procedure and aim of the interview		
Checking the quota criteria	Socio-demographic data of the interviewee	Household/family situation Field of diagnosis	Educational background Job description/field of activities State of knowledge of the SiKOM project
Introductory questions	Definition of CM Attitude towards CM Relevance of CM in (clinical) everyday life	Guiding question: What do you understand by CM? Maintenance question: What else counts as CM for you?	
		What role does CM play in your everyday life? To what extent do you use CM? Can you give an example? To what extent do you ask your doctor about CM? Have there already been conflicts in regard to CM and your child’s current therapy?	What role does CM play in your clinical life? To what extent do parents ask you about CM? To what extent are CM therapies used in your clinic? Can you give an example? Have there already been conflicts in regard to CM and the current therapy of your patients?

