### Data analysis

4.5

Frequent communication between the project team and contact persons at the respective pediatric oncology departments and the parents, as well as the regular on-site monitoring of the study team, will ensure the correctness and quality of the data generated. All parent and staff questionnaires from the five centers are stored separately from the consent forms. The questionnaires to be evaluated are only available to the statistician in a pseudonymized form. Pseudonymization involves the removal of personal identifiers and their substitution with placeholder values, typically composed of a sequence of numbers and letters, so it is not possible to draw conclusions about the individual participants. The data analysis is carried out by IBM® SPSS. The questionnaires are entered manually into SPSS and checked for transmission errors using the dual control principle with the original data.

Qualitative data will be audio-recorded, transcribed verbatim, anonymized, and then coded and analyzed according to qualitative content analysis (43, 44) using MAXQDA software. The analysis follows an inductive approach, as the categories were independently developed based on our research question.

To evaluate the feasibility and determine whether the intervention is suitable for progression to a larger effectiveness trial, specific progression criteria have been established. Recruitment feasibility will be assessed by the ability to recruit the planned sample size of 100 medical staff and 50 parents within the study period, with an acceptable participation rate and minimal refusal. Retention rates are also critical, with at least 80% of participants expected to remain engaged throughout the study, and reasons for dropouts systematically documented. The acceptability of the intervention will be evaluated using the Acceptability of Intervention Measure (AIM) and qualitative feedback, with positive feedback from at least 70% of participants serving as a benchmark.

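### The AIM, a named source for the 70% acceptability benchmark, leaves out waitlist parents who are counseled after their only questionnaire

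*Protocol article*

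**What the plan says.** Under Study setting and design (3.1), the parent sample is 50, in two cohorts of 25, with 10% dropout expected. Assignment is not randomized: the control cohort is run first, then the intervention cohort. The Figure 1 caption says that the processes run consecutively and separately in each center. One cohort is counseled and "the other will serve as a waitlist cohort to be offered the respective CM counseling after the outcome assessment". On timing, "parent cohorts will receive standard questionnaires three weeks after study inclusion", and "For the parent control cohort, the CM counseling will take place after this outcome assessment, while the parent intervention cohort will receive CM counseling before". Under Outcomes (4), "Both cohorts of parents receive one questionnaire each".

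Under Feasibility (4.1), item 3 reads "Acceptability of the CM intervention (parent intervention cohort only), assessed with the Acceptability of Intervention Measure". Item 5 of the same list has a second acceptability instrument, the TFA, given to a targeted sample of parents and staff with no cohort named.

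On interviews the article says two things. Secondary outcome (4.4) states that "qualitative data will be assessed using semi-structured interviews of the parent intervention cohort and medical staff". Primary outcome (4.3) speaks of interviewing both parent cohorts as well as staff, before and after training.

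Under Data analysis (4.5), acceptability is judged on the AIM and qualitative feedback, "with positive feedback from at least 70% of participants serving as a benchmark".

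**The concern.** Acceptability is part of the main objective (section 2), and the 70% benchmark is one of the criteria for deciding whether a larger trial is warranted. The waitlist design offers both cohorts the same counseling, yet only one cohort rates it on the AIM. A waitlist parent's one questionnaire precedes the session, so it cannot rate the session either. If section 4.4 governs the interviews, both named sources for the benchmark exclude counseled waitlist parents.

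Two things are at stake. The first is precision: the benchmark rests on at most 25 ratings when up to 50 could be had from parents already enrolled. The second is coverage: because the control cohort comes first in each center, the parents without a rating are probably among the first families counseled there.

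**Working it through.** **Inputs from the article.** 50 parents = 25 + 25, which reproduces; 10% dropout (3.1); benchmark 70% (4.5). The article gives no power calculation for this criterion, so there is none to reproduce.

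**Who can rate.** For control parents the order is inclusion, questionnaire at three weeks, then counseling if accepted. With one questionnaire per parent and the AIM limited to the other cohort, their number of AIM ratings is zero by design.

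**Share of counseled parents left out.** Let u be uptake in the waitlist cohort relative to the intervention cohort. The share is 25u / (25 + 25u). The article gives no value for u, so these are assumptions:
- u = 1: 25/50 = 50%
- u = 0.75: 18.75/43.75 = 43%
- u = 0.5: 12.5/37.5 = 33%
- u = 0.25: 6.25/31.25 = 20%

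**Number of ratings.** Intervention cohort only: 25 × 0.9 = 22.5, so 22 or 23. Both cohorts at full uptake: 50 × 0.9 = 45. At half waitlist uptake: 22.5 + 11.25 = 33.75, so 33 or 34.

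**Precision near 70% (95% Wilson interval).**
- 15/22 (68.2%): 47.3% to 83.6%, width about 36 points
- 31/45 (68.9%): 54.3% to 80.5%, width about 26 points

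Exact Clopper-Pearson intervals, at the smallest count that meets the benchmark, show the same pattern: 16/22 gives 49.8% to 89.3%, and 32/45 gives 55.7% to 83.6%.

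**Chance of meeting the benchmark.** P(X ≥ r) for X binomial(n, p), where r is the smallest whole number of at least 0.7n:

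| n | r | p = 0.60 | p = 0.80 |
|---|---|---|---|
| 22 | 16 | 15.8% | 86.7% |
| 23 | 17 | 12.4% | 84.0% |
| 25 | 18 | 15.4% | 89.1% |
| 33 | 24 | 9.2% | 89.3% |
| 34 | 24 | 13.8% | 93.8% |
| 45 | 32 | 8.4% | 94.8% |
| 50 | 35 | 9.6% | 96.9% |

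The values do not move smoothly with n, because r must be a whole number. The fair comparison is therefore between ranges. With one cohort (n = 22 to 25) a true 60% passes with probability 12–16%, and a true 80% with 84–89%. With both cohorts at full uptake (n = 45 to 50) the figures are 8–10% and 95–97%. At half uptake a true 60% passes with 9–14%, which overlaps the one-cohort range.

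**The case against.** The restriction can be defended. Intervention parents receive the counseling as planned, before the three-week assessment. Waitlist parents receive it later and after answering a questionnaire about complementary medicine, so pooling mixes two situations. The AIM in 25 intervention parents still answers the acceptability question for counseling delivered on schedule. The study is exploratory, and an unmet criterion leads to modification and reassessment. The article itself stresses how much paperwork these parents carry. All of this stands. It keeps the point modest and is the reason for reporting by cohort.

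A reader might infer that waitlist parents are never asked about the counseling and contribute nothing on acceptability. The article does not support that. The TFA sample is not limited to one cohort, section 4.3 has both parent cohorts interviewed, and the counts of parents counseled and of planned sessions completed are not restricted by cohort. None of this closes the AIM gap: section 4.5 does not name the TFA as a source for the benchmark, and sections 4.3 and 4.4 disagree.

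A reader might also infer that exactly half of the counseled parents are lost. Counseling is only offered to the waitlist cohort, so half is the upper end, reached at equal uptake.

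Finally, a reader might infer that the benchmark is biased upward because start-up problems go unrated. Nothing in the article gives a direction or size for such an effect. Waitlist sessions take place at an unstated time after the three-week questionnaire and could overlap the first intervention sessions; Figure 1, which might settle the order, is not available here. Staff interviews, the session-completion target and the fidelity checklist do not exclude waitlist sessions.

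**Conclusion.** The point holds as a matter of precision and coverage. By the article's own wording, waitlist parents who take up counseling give no AIM rating, so that source for the 70% benchmark rests on about 22 to 25 parents when up to 45 to 50 could be available. At full uptake and response, the 95% interval near 70% narrows by about 10 points (36 to 26), and the chance of passing at a true 60% falls from 12–16% to 8–10%. These figures assume the stated 10% dropout, independent ratings, and equal acceptability in the two cohorts. At half uptake the interval gain is smaller, and the reduction in wrongly passing may largely disappear. The article's estimate that about 50% of distributed questionnaires come back completed is a reason not to count on the full gain.

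The criterion is not invalid as it stands. The change is a modest, inexpensive improvement, and the conflict between sections 4.3 and 4.4 needs settling in any case.

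**What to change.** - Give waitlist parents the AIM after their counseling, at the same interval after counseling as in the intervention cohort.
- Report acceptability by cohort and for all counseled parents against the 70% benchmark, with the number offered counseling, the number counseled and the number rating in each cohort.
- Reconcile sections 4.3 and 4.4 on which parents are interviewed, so that counseled waitlist parents can be included, and state whether the TFA sample covers them.
- If the AIM restriction is kept, give the reason and limit the acceptability conclusion to the intervention cohort.

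The cost is one short extra form for up to 25 parents already enrolled, with some non-return and a small added burden on families under strain. No new participants are needed. The form follows the waitlist parents' outcome questionnaire, so the comparison between cohorts is unaffected. Because waitlist parents are counseled later, the pooled figure should never be shown without the two cohort results.
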